All interviews will be transcribed verbatim, and all participant data will be pseudo-anonymised by assignment of a unique study identifier (until completion of follow-up interviews, thereafter all interview data will be completely anonymised). A thematic analysis will be conducted following a six-step process and employing Normalisation Process Theory (NPT) [26] to understand how the intervention was (or was not) embedded in routine clinical practice, and relational coordination [27] to explore interprofessional collaboration. NPT is concerned with understanding the dynamics of implementing, embedding, and integrating a complex intervention within a healthcare system. NPT has four components which can be used to evaluate implementation of complex interventions, these components are coherence, cognitive participation, collective action and reflexive monitoring. Coherence encompasses whether the intervention makes sense to, and is perceived to be of value to, the relevant participants, and whether it fits with the goals and activities of the organisation. Cognitive participation considers whether participants will be prepared to invest in the new intervention. Collective action asks what effect the intervention will have on current work and whether it is consistent with the existing practices. Finally, reflexive monitoring asks how participants perceive the intervention once it has been in place for a while [26]. Contextual factors and potential barriers relating to the mixed public and private funding of Irish Primary Care will also be explored. Researchers will independently review the transcripts of the individual interviews several times to familiarise themselves with the relevant data. Small sections of data will be assigned a code that summarises the content. Codes with common features will be grouped together in emerging themes, before finally being assigned to overarching themes [28]. In the write-up, quotations will be used as exemplars of key themes. NVivo 10® will be used to index and organise the data for analysis. In addition, demographic characteristics of the pharmacists and GPs involved will be displayed and taken into account in the analysis process. Moreover, the potential timesaving (or time-intensification) aspects of the intervention will also be explored during the process evaluation. However, given the small sample size, this cannot be accurately determined.

### Economic analysis

A cost of care study will be conducted alongside the pilot study to determine the direct costs and related cost savings of the proposed intervention. Comparator cost data will be available from the control group of the parallel SPPiRE trial [18] and the national PCRS prescribing reimbursement data. The completion of a costing study will allow us to consider potential cost-effectiveness and will guide a future cost-effective analysis (as a secondary outcome measure), if an RCT is carried out. The costing study will be based on the cost of providing the intervention and the cost savings realised from the intervention. Costs related to the recruitment and training of the pharmacists, practiced-based education of the GPs and associated staff will also be accounted for. Data used in the economic analysis will include:Cost of changes to prescriptions to address prescribing that is high risk or potentially inappropriate, as documented by the pharmacist;Cost of deprescribing by calculating original cost of prescriptions and final cost due to changes in the items prescribed;Cost savings on the number of items changed from branded to generic prescribing;Cost savings on the number of preferred drugs which have been switched from other agents;Cost savings following assessment of requirement for commonly used preventive drugs such as aspirin and cholesterol-lowering agents;Resources used in the reviewing of nursing (residential) home patients and changes to prescriptions will be measured and costed;Reduced wastage of medicines due to rationalising polypharmacy will be measured and the associated cost ascertained.

### Continuation criteria

Continuation criteria (see Table 2) will be considered to determine whether further evaluation of this intervention is warranted (to test the effectiveness of the intervention). Continuation criteria (also referred to as progression criteria) are based on consideration of the primary objectives around feasibility and the potential for effectiveness and system-wide implementation. Quantitative and qualitative process evaluation data will be analysed to consider the following continuation criteria:Successful general practice uptake and recruitment and retention of pharmacists;Successful implementation of the intervention and consideration of treatment fidelity criteria [29];Process evaluation indicates that the intervention is acceptable to general practice teams and patients;Positive effect on medicines-related outcomes;Cost of care study indicates that the intervention might be cost saving.

**Table 2 Tab2:** Continuation criteria which indicate whether to proceed with a randomised controlled trial

Proceed with RCT	Proceed with RCT following some changes to the protocol	Do not proceed with RCT unless problems can be overcome
Recruitment of 4 general practices within 3 months	Recruitment of 4 general practices within 3–6 months	Unable to recruit 4 general practices within 6 months
Retention of ≥ 3 general practices throughout 6-month intervention period	Retention of 2 general practices throughout 6-month intervention period	Retention of < 2 general practices throughout 6-month intervention period
Recruitment of 3 pharmacists within 3 months	Recruitment of 3 pharmacists within 3–6 months	Unable to recruit 3 pharmacists within 6 months
Retention of ≥ 2 pharmacists throughout 6-month intervention period	Retention of 1 pharmacist throughout 6-month intervention period	Retention of 0 pharmacists throughout 6-month intervention period
Recruitment of 50 PROM study patients from each practice	Recruitment of 25–49 PROM study patients from each practice	Recruitment of < 25 PROM study patients from each practice
Retention of ≥ 35 PROM study patients for follow-up	Retention of 25–34 PROM study patients for follow-up	Retention of < 25 PROM study patients for follow-up
GPP intervention acceptable to ≥ 75% GPs, pharmacists and patients involved	GPP intervention acceptable to 50–74% GPs, pharmacists and patients involved	GPP intervention acceptable to < 50% GPs, pharmacists and patients involved
Delivery of GPP intervention feasible	Delivery of GPP intervention partially feasible	Delivery of GPP intervention not feasible
GPP intervention demonstrates cost savings which outweigh the cost of implementing the intervention	GPP intervention demonstrates potential for cost savings which outweigh the cost of implementing the intervention	GPP intervention does not demonstrate potential cost savings which outweigh the cost of implementing the intervention

*GP* general practitioners, *GPP* general practice pharmacist, *PROM* Patient Reported Outcome Measures, *RCT* randomised controlled trial

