### Main study population and recruitment

The study will be conducted in four general practices. Practices eligible for invitation to the study will be identified from the Health Research Board (HRB) Centre for Primary Care Research (CPCR) in Ireland research network. Practices will be eligible to participate if they have ≥ 1000 older patients (aged ≥ 65 years) on their patient panel. This will ensure adequate numbers of patients with significant polypharmacy (defined here as ≥ 10 repeat medicines) and allow the feasibility of the intervention to be tested in the nested PROM study. Practices will be purposively selected to reflect a range of practice sizes and types, from both socioeconomically deprived and affluent areas. Eligible practices will be invited to participate via a letter of invitation sent to the practice by email. The invitation email will include a study information pack which consists of a study information leaflet outlining the steps of the intervention and availability of continuing medical education points for participation in the study, practice profile questionnaire and practice consent form.

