### Nested PROM study population and recruitment

Using a tool embedded within the general practice prescribing software, the pharmacist will compile a list of patients with significant polypharmacy (defined as ≥ 10 repeat medicines). A random sample of these patients will be selected by the pharmacist and screened for inclusion in the nested PROM study. Patients will be eligible for inclusion in the nested PROM study if they are aged ≥ 65 years and are able to attend their practice or participate in data collection. Patients will be excluded if they have psychiatric or psychological morbidity or cognitive impairment sufficient to impair the provision of informed consent, if they have a life-limiting illness likely to lead to death or major disability during the study follow-up period, or if they have already had a medication review/interacted with the pharmacist during the study period.

A letter of invitation (printed on practice headed paper) and a patient information pack will be posted to eligible patients. The patient information pack will include a study information leaflet, consent form and questionnaire to explore their perceived level of health. The letter of invitation will invite them to attend an appointment with the pharmacist for a medication review; they will also be asked to bring their completed questionnaire to this appointment. Eligible patients will be invited until a total of 200 patients (50 patients from each practice) are recruited. Written informed consent will be obtained from these patients (by the pharmacist) prior to any data collection, and follow-up questionnaires will be sent to these patients 6 weeks after the pharmacist has left the practice. Figure 1 gives an overview of the flow of patients through the study.

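### Table 2's PROM retention row is a count with no stated unit or denominator, and it misclassifies retention read study-wide or per practice; the recruitment row has no rule for practices in different bands

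*Protocol article*

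**What the plan says.** The section on the nested PROM study population fixes the target: "Eligible patients will be invited until a total of 200 patients (50 patients from each practice) are recruited". The main study section gives the number of practices: "The study will be conducted in four general practices".

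Table 2 (Continuation criteria) has three columns: proceed with an RCT, proceed after some protocol changes, and do not proceed unless the problems can be overcome. They are called green, amber and red below; the labels are mine. Two rows concern PROM patients.

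- **Recruitment.** Green is "Recruitment of 50 PROM study patients from each practice". Amber is 25 to "49 PROM study patients from each practice". Red is fewer than "25 PROM study patients from each practice".
- **Retention.** Green is at least "35 PROM study patients for follow-up". Amber is 25 to "34 PROM study patients for follow-up". Red is fewer than 25.

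The per-practice qualifier stands in all three cells of the recruitment row and in none of the retention row. The retention row has no percentage and does not refer to the number recruited. The acceptability row of the same table does use percentages. No other section supplies the missing unit or says how practices in different recruitment bands are to be classified.

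**The concern.** Retention is a proportion: those followed up out of those recruited. A fixed count stands in for it only when the number recruited is known and fixed. Here the unit is unstated, and the number recruited is expected to vary, since the table itself provides an amber band of 25–49 per practice. Once recruitment falls into that band, a per-practice count marks the study down a second time for low recruitment and says little about whether patients stay.

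The recruitment row has a different and lesser fault. Its unit is clear, but each column describes one band holding in every practice. Practices are chosen on purpose to differ in size, type and area deprivation, so unequal recruitment is foreseeable.

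The article says the study will inform whether an RCT is indicated, and it has no formal sample size calculation and no formal comparison group. The thresholds in Table 2 therefore carry much of the prespecified basis for that decision. If the unit, denominator and classification rule are open, they will be chosen after the results are known.

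**Working it through.** **Inputs.** Four practices (main study section); 50 PROM patients per practice (nested PROM section); retention cut-offs 35 and 25, recruitment cut-offs 50 and 25 (Table 2).

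**Reproducing the plan's own figure.** 4 × 50 = 200, as stated.

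**Formula.** Retention rate = number retained ÷ number recruited.

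**Reading 1: the retention count is study-wide, with 200 recruited.**

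- Lowest green: 35/200 = 17.5%.
- Amber: 25/200 = 12.5% to 34/200 = 17%.
- With only 25 recruited in each practice (4 × 25 = 100), the highest red rate is 24/100 = 24%. A 24% rate can therefore be red at low recruitment while 17.5% is green at full recruitment.

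**Reading 2: the retention count is per practice.**

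| Recruited in the practice | Rate needed for green | Rate needed for amber | Colour at 100% retention |
|---|---|---|---|
| 50 | 35/50 = 70% | 25/50 = 50% | green |
| 49 | 35/49 = 71.4% | 25/49 = 51.0% | green |
| 40 | 35/40 = 87.5% | 25/40 = 62.5% | green |
| 35 | 35/35 = 100% | 25/35 = 71.4% | green |
| 30 | not reachable | 25/30 = 83.3% | amber |
| 25 | not reachable | 25/25 = 100% | amber |

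At 25 recruited, losing one patient gives 24/25 = 96% and a red result. For any practice recruiting 25 to 34, green is out of reach whatever the follow-up. At 50 recruited the row gives the sensible 70% and 50%.

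**Recruitment row.** Each practice can fall in one of three bands, so four practices give 3⁴ = 81 combinations. Only three are uniform (all green, all amber, all red), so 81 − 3 = 78 match no column read literally. This counts patterns; it is not a probability. Two examples:

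- 50/50/50/49, total 199. It fits no column literally, but few readers would hesitate to call it amber.
- 50/50/50/20, total 170. It fits no column literally. By the worst practice (20) it is red; by the mean, 170/4 = 42.5, it is amber. Here the choice of rule changes the result.

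**The case against.** The strongest reply is that the intent is plain. The row directly above is per practice, shares the cut-off of 25, and every PROM target is 50 per practice, so 35 and 25 most likely mean 70% and 50% of 50. The criteria are also only to be considered, alongside fidelity, acceptability, qualitative findings and cost, and the red column leaves room for problems to be overcome. Much of this stands. It makes the study-wide reading the less likely one, and it means no result follows mechanically from the table. It does not rescue the row, because the per-practice reading still misfires across the amber recruitment band that the table foresees.

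Some stronger inferences are tempting and should not be drawn:

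- **That one table calls 17.5% green and 96% red at once.** The two figures need incompatible readings: the first is study-wide with 200 recruited, the second per practice with 25 recruited.
- **That PROM recruitment has no time limit.** The row gives none, but the sections on study design, intervention components and PROM data collection all place the PROM work in months 4 and 5.
- **That calling the loss of one practice green contradicts the recruitment row.** Separate rows may show different colours. What is open is only whether a withdrawn practice counts as one of the practices.
- **That recruitment and retention rates could not be reported.** Decision cut-offs do not limit reporting, and each PROM participant has a study identifier used for follow-up.

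**Conclusion.** The point holds for the retention row. Under the study-wide reading it is far too lenient (green from 17.5% of the target number). Under the likelier per-practice reading it is right at 50 recruited and increasingly wrong below that: 96% retention can be red, and green is impossible with 25–34 recruited. The missing rule for mixed recruitment bands is a real but secondary gap, which matters for patterns such as 50/50/50/20 and hardly at all for 50/50/50/49.

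Severity is moderate. No patient-level estimate depends on these rows, and the criteria guide judgement, but they are stated thresholds for a go/no-go decision and can point the wrong way. The conclusion rests on the wording of Table 2 and on recruitment possibly falling below 50 in some practice, which the table itself allows for. That 70% and 50% were intended is an inference from 35/50 and 25/50; the article does not say so.

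**What to change.** **Retention.** Define it as follow-up questionnaires returned divided by PROM patients recruited, pooled over practices. Use contiguous bands: green at 70% or more, amber from 50% to below 70%, red below 50%. At full recruitment these are 140/200 and 100/200. Bands in whole percentages would leave a gap: 139/200 = 69.5% would fall between 69 and 70. Report the rate for each practice beside the pooled figure. The investigators should confirm that 70% and 50% are what they meant.

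**Recruitment.** Keep the cut-offs of 50 and 25 and state one rule that covers every pattern, for example green if every participating practice reaches 50, red if any is below 25, amber otherwise. Under it 50/50/50/49 is amber and 50/50/50/20 is red. A mean over practices is a poorer choice: 50/50/50/0 averages 37.5 and would read amber although one practice recruited nobody, and 49.75 would fall between the present bands. Say whether a withdrawn practice counts.

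**Timing and cost.** The change rewords two rows and needs no new data. The article reports that PROM recruitment and data collection are already underway, so the cost is a documented change to a progression criterion in mid-study. Record it as a dated clarification, made before follow-up results are seen.

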### Data management and protection

A data management plan will be developed and agreed by the study steering committee. Practice-level data will be collected from patient health records and will be completely anonymised. PROM data will be collected using patient health records, completed questionnaires and self-reporting (during the medication review). These data will be pseudo-anonymised since contact details will be required for patient follow-up and interview (with patient consent). A unique study identifier number will be given to each PROM participant (this will be recorded in the data collection tool for baseline PROM data collection). In a separate document, the study identifier number and participant’s contact information will be recorded. These data will be used for study follow-up purposes only and will only be accessed by the pharmacist at that practice. No PROM data will leave the practice during the intervention period. Upon completion of the follow-up with each PROM participant, PROM study data will also be completely anonymised. Thereafter, it will leave the practice for analysis.

Qualitative evaluation data will be collected via pre- and post-intervention semi-structured interviews which will be audio recorded and transcribed verbatim. Similarly, data collected during the pre-intervention interview will be pseudo-anonymised until the post-intervention follow-up interviews have been conducted. Thereafter, all interview data will be completely anonymised.

All practice and PROM data will be stored electronically on secure password-protected hard drives and transferred to a secure password-protected server. Hard copies of data (i.e. completed questionnaires and consent forms) will be scanned and stored electronically on a secure password-protected server; the original copies will be shredded. Completed, anonymised questionnaires will only leave the practice on completion of follow-ups. Audio-recordings will be transcribed and stored electronically and the original recording deleted; all transcripts will be completely anonymised. The principles of FAIR data will be applied when considering outcomes for follow-up studies in this area.

### Ethical approval

Ethical approval was granted by the Research Ethics Committee of the Irish College of General Practitioners.

## Discussion

This study aims to test an intervention (GPP intervention) involving pharmacists, working within GP practices, to optimise prescribing in a mixed public and private primary healthcare system in Ireland. The intervention will focus on patients aged ≥ 65 years with significant polypharmacy (≥ 10 repeat medicines) and will utilise a number of methodologies including the review of community-based and nursing (residential) home patients for instances of prescribing practices considered to be high risk or potentially inappropriate, use of preferred drugs and generic prescribing and assessment of the need for commonly prescribed preventive medicines. This research aims to increase the quality of prescribing in primary care, support the potential for interprofessional collaborations in primary care and contribute cost savings to the payer (i.e. the HSE) and the patient. The study will assess the feasibility of implementing processes to (a) improve appropriate prescribing in primary care and reduce PIP, (b) evaluate the costs associated with the intervention and (c) follow patient-reported outcome measures to determine changes in patient wellbeing and satisfaction with the intervention.

Most of the older people in Ireland are living independently in the community, and approximately 13% of people living in Ireland are aged ≥ 65 years [30]. This has implications for the prevalence of multimorbidity, frailty, polypharmacy and other symptoms associated with ageing, though multimorbidity and polypharmacy are increasingly an issue across the age spectrum [31]. A pharmacist, based in general practice, is ideally situated to support the management of these complex patients. An intervention such as this could enhance collaboration between healthcare professionals, improve medicines management for individual patients and improve health outcomes through safer and more effective medicines management [32].

Despite the relatively widespread implementation of practice-based pharmacists in the UK, there is limited evidence on the clinical- and cost-effectiveness of this type of intervention to date. Moreover, there are significant differences between the general practice settings that exist in the UK (publicly funded) and other countries such as Ireland (mixed publicly and privately funded). Therefore, this study has potential national and international impact and importance. Furthermore, this research has the capacity to provide a safer and higher quality service to patients by targeting outcomes at an early stage in primary care and introducing medicines management interventions that will have an additive effect on services and programmes both locally and nationally.

### Study status

At the time of this publication, four general practices and three clinical pharmacists have been recruited. Pre-intervention interviews have been undertaken with the GPs and pharmacists involved. The intervention period has started in each of the four practices, and practice-level data collection is on-going. PROM patient identification and recruitment and PROM data collection are underway.

## Abbreviations

A&E: Accident and emergency
ADR: Adverse drug reaction
CPCR: Centre for Primary Care Research
GP: General practitioner
GPP: General practice pharmacist
HRB: Health Research Board
HSE: Health Service Executive
MMP: Medicines Management Programme
MRC: Medical Research Council
NHS: National Health Service
PIP: Potentially inappropriate prescribing
PROM: Patient Reported Outcome Measures
RCT: Randomised controlled trial
SD: Standard deviation
UK: United Kingdom
